#### 6.6.4.2 Urine screen for drugs of abuse

Urine will be collected at Screening and Baseline for drugs of abuse listed in APPENDIX 3 (Cohort A) and APPENDIX 4 (Cohort B).

#### 6.6.4.3 Alcohol breath test

An alcohol breath test will be performed at Screening and Baseline, as specified in the SOA (APPENDIX 1) Cohort A and APPENDIX 2 (Cohort B).

#### 6.6.4.4 Pregnancy tests

Blood will be collected at Screening for a serum pregnancy test to be performed by the local clinical laboratory. Urine will be collected at Baseline and the EOT/ET Visit (Visit 4) for a urine pregnancy test to be performed by the local clinical laboratory.

## 6.7 Collection and Reporting of Adverse Events

AEs including SAEs will be monitored by nonleading questions posed to subjects at each study visit. AEs will be graded by seriousness, severity, and relationship to the study drug for the duration of the study. The PI or delegate will routinely review laboratory results for any clinically significant abnormal results that may represent potential AEs and document any findings in the source documents.

In the event that any subject experience an AE that is considered by the PI to be possibly, probably, or definitely related to study drug and that is severe or medically significant, that subject should be discontinued from further study drug administration and monitored for resolution of the event. Study drug should be discontinued regardless of other factors such as threat to life or admission to hospital.

In the event that 3 subjects experience the same AE meeting the criteria described above or when 2 subjects experience the same AE that is life-threatening or requires immediate intervention to prevent death and that is attributed to study drug, enrollment in the study should be temporarily halted to allow further evaluation.

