#### 8.2.1.1 Study termination

Intake of study drug may be halted if the Sponsor/Medical Monitor determines there is any unexpected, significant, or unacceptable risk to subjects upon ongoing review of aggregate safety data; the Sponsor will inform the PI within 24 hours after this determination.

This study may be suspended or prematurely terminated by the Sponsor if there is sufficient reasonable cause. Written notification, documenting the reason for study suspension or termination, will be provided by the Sponsor to the PI. If the study is prematurely terminated or suspended, the PI will promptly inform the IRB/IEC and will provide the reason(s) for the termination or suspension. Circumstances that may warrant termination or suspension of the conduct of the study include, but are not limited to the following:

- Determination of unexpected, significant, or unacceptable risk to subjects, as determined by the ongoing review of aggregate safety data by the Sponsor/Medical Monitor;
- Insufficient compliance with protocol requirements by study sites;
- Consistently insufficient, incomplete, and/or unevaluable data submission by the study sites;
- 3 subjects develop the same CTCAE Grade 3 AE determined as related to study drug;
- 2 subjects develop any CTCAE Grade 4 AE determined as related to study drug; OR • 1 subject develops a CTCAE Grade 5 AE regardless of its relationship to the study drug.

In the event of a potentially related Grade 5 event or Suspected Unexpected Serious Adverse Reaction (SUSAR), available information will be reviewed which includes the potential of unblinding the subject, and will communicate this information to the unblinded Chief Medical Officer for determination on any potential modification of study procedures to insure subjects’ safety, which may or may not include termination of the study. Review of the potentially related Grade 5 events or SUSARs will occur within 48 hours of the Sponsor making the determination that the event may be related to study drug.

Reporting requirements are outlined in the study Safety Monitoring Plan, including the timelines for completion by study sites and submission to the appropriate regulatory agencies.

If the study is suspended temporarily, the study may resume once concerns about safety and tolerability, protocol compliance, and/or data quality are addressed and satisfy the Sponsor, regulatory authorities, and/or IRB/IEC (including approval of a substantial amendment, if required).

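### The enrollment-halt rule in 6.7 is narrower than the Sponsor's own list in 8.2.1.1: it omits two different related life-threatening AEs and any death

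*Protocol*

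**What the plan says.** Section 6.7 gives two conditions under which "enrollment in the study should be temporarily halted to allow further evaluation". The first is three subjects with the same drug-related AE that is severe or medically significant, which is the Grade 3 wording of 6.7.3.1. The second is that "2 subjects experience the same AE that is life-threatening or requires immediate intervention to prevent death and that is attributed to study drug", which corresponds to Grade 4. Death is not mentioned.

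Section 8.2.1.1 has a separate list, introduced by "Circumstances that may warrant termination or suspension of the conduct of the study include, but are not limited to the following". It has three severity entries:

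- The Grade 3 entry reads "3 subjects develop the same CTCAE Grade 3 AE determined as related to study drug", the same count and the same condition as in 6.7.
- The Grade 4 entry reads "2 subjects develop any CTCAE Grade 4 AE determined as related to study drug", with no condition that the AEs be identical.
- The Grade 5 entry reads "1 subject develops a CTCAE Grade 5 AE regardless of its relationship to the study drug", which has no counterpart in 6.7.

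The same section allows for a temporary stop ("If the study is suspended temporarily, the study may resume once concerns about safety and tolerability" and related matters are addressed). It also sets a review step: "Review of the potentially related Grade 5 events or SUSARs will occur within 48 hours of the Sponsor making the determination" of a possible link to the drug. The information goes to the unblinded Chief Medical Officer, who decides whether study procedures should change.

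**The concern.** A pause in enrollment is the milder and more easily reversed action, and suspension or termination of the study the heavier one. One would expect any event pattern that can justify the heavier action also to prompt the milder one while the facts are gathered. For Grade 3 it does, because the two sections use the same count and the same requirement for identical AEs. For Grade 4 the count is two in both sections, but 6.7 requires the same AE and 8.2.1.1 accepts any. For Grade 5, 8.2.1.1 has an entry and 6.7 has none.

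At stake is whether new subjects are randomized while two dissimilar related life-threatening events, or a possibly drug-related death, are being evaluated. As written, that depends on a Sponsor decision and not on a stated rule. The point concerns subject safety only and does not touch the sample size or the efficacy analysis.

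**Working it through.** The protocol states no figure to reproduce here, so the main check sets the rules side by side. Sources are 6.7 and 8.2.1.1, with severity wording mapped to grades through 6.7.3.1.

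| Pattern | 6.7 enrollment halt | 8.2.1.1 suspension or termination | 48-hour review |
| --- | --- | --- | --- |
| 3 subjects, same related Grade 3 AE | should | may | only if a SUSAR |
| 2 subjects, same related Grade 4 AE | should | may | only if a SUSAR |
| 2 subjects, different related Grade 4 AEs | not stated | may | only if a SUSAR |
| 1 potentially related death | not stated | may | yes |
| 1 death judged unrelated | not stated | may | no |

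The gap is the third, fourth and fifth rows. A single death can never reach a count of two or three, whatever the event rate.

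**Illustration for the third row.** The per-subject rate p of a related Grade 4 AE and the number K of equally likely AE terms are assumptions, as is at most one such AE per subject. N is 25 if only active subjects are at risk (20 + 5 from section 7.1), or 50 if all are (40 + 10).

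Given exactly two subjects with a related Grade 4 AE:

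P(different terms) = 1 − 1/K = 67%, 80% and 90% for K = 3, 5 and 10.

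This is lower if one term dominates.

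Unconditionally:

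- P(any two) = 1 − (1−p)^N − Np(1−p)^(N−1)
- P(same two) = 1 − Σ_n Binom(n; N, p) × Π_{i<n} (K−i)/K
- Gap = P(any two) − P(same two)

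Example with N = 25, p = 1%, K = 5: P(any two) = 1 − 0.7778 − 0.1964 = 0.0258. P(same two) = 0.0058. The gap is 0.0200.

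| Assumed p | Gap, N = 25, K = 5 | Gap, N = 50, K = 5 |
| --- | --- | --- |
| 0.5% | 0.5% | 2.0% |
| 1% | 2.0% | 6.7% |
| 2% | 6.6% | 18.1% |
| 5% | 23.4% | 34.3% |

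These figures show how the wording behaves under assumed rates. They are not evidence of how large the gap is in this trial. Section 1.7 describes a benign safety record, so 5% is a high bound. The calculation also spans the whole trial, although section 1.5.2.3.2 shows that part of Cohort A's exposure is already past.

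**The case against.** A reader might infer that the halt rule is mis-ordered by severity, or that the two sections contradict each other. The documents support neither reading. Within 6.7 the count falls from three to two as severity rises. Within 8.2.1.1 it falls from three to two to one. An inversion appears only if the *should* of one section is set against the *may* of the other, and those words govern different actions. Compared like for like, three identical Grade 3 AEs are also only a *may* in 8.2.1.1.

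The stronger objection is that the severe cases already have a process. A life-threatening AE is serious under 6.7.2, and under 6.7.3.3 it is unexpected unless listed in the Investigator's Brochure. Given the record in 1.7, the first related life-threatening AE would probably be a SUSAR and go to the 48-hour review before any second event occurred. The Brochure is not available, so this is likely but not certain. In addition, 6.7 takes a subject with a related severe AE off study drug, 4.5.2 lists Grade 4 or higher as a ground for stopping that subject's drug, and 8.2.1.1 provides ongoing aggregate review with power to halt dosing.

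Most of this stands, and it is why the practical effect is small. It does not close the gap. The 48-hour review states no enrollment pause while it runs, and its clock starts only once the Sponsor has judged the event possibly related. The subject-level rules act on the affected subject's drug and not on enrollment. Aggregate review and suspension are discretionary.

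It is also fair to object that an automatic halt after every death would override Sponsor judgement in clearly unrelated cases. That is accepted, and the fix leaves such deaths out.

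**Conclusion.** The point holds as a gap in coverage. Followed literally, 6.7 does not pause enrollment for two different related Grade 4 AEs or for a death, although 8.2.1.1 treats both as possible grounds for suspending or ending the study. The conclusion rests on the text of those two sections and needs no assumed rate. Its practical size is small and cannot be estimated from the protocol, because a temporary suspension is already permitted and most such events would probably reach the 48-hour review. This is an inexpensive safety improvement worth considering, and not an error that endangers the trial's conclusions.

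**What to change.** In 6.7, state that enrollment is halted temporarily pending evaluation after either of the following:

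- two subjects with any related Grade 4 AE, whether or not it is the same AE
- one potentially related Grade 5 AE, until the 48-hour review is complete

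Add a cross-reference to 8.2.1.1. Leave the Grade 3 count as it is, do not narrow 8.2.1.1, and leave a death judged unrelated to Sponsor discretion there.

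The cost is one sentence, a cross-reference and a few more short, reversible pauses. The extra Grade 4 pauses equal the gap computed above. Under an assumed 1% rate and 3 to 10 terms, the chance of one rises by 1.6 to 2.3 percentage points with 25 subjects at risk, or 5.3 to 7.8 points with 50. At the high-bound 5% rate the increases would be 17.4 to 29.0 and 22.3 to 48.6 points. Pauses for potentially related deaths come on top and are not quantified.

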### 6.7.1 Adverse event and treatment-emergent adverse event

As defined by the International Council for Harmonisation (ICH), an AE is any untoward medical occurrence in a patient or clinical investigation subject who consumes a study drug, which does not necessarily have a causal relationship with the study drug. An AE can, therefore, be any unfavorable and unintended sign (including an abnormal laboratory finding), symptom, or disease temporally associated with the use of a medicinal (investigational or test) product, whether or not considered related to the study drug.

A TEAE is defined as any AE that begins or worsens in severity after the first dose of study drug is taken.

If an abnormal laboratory result or vital sign is recorded and deemed a clinically significant change compared to the baseline value(s), the PI will also report these findings as an AE.

AEs leading to discontinuation or reduction in intake of study drug will be reported as AEs of interest within the standard AE reporting timeframe.

### 6.7.2 Serious adverse event

An AE is considered “serious” if, in the view of either the PI or the Sponsor, it results in any of the following outcomes:

- Death
- A life-threatening condition
- Inpatient hospitalization or prolongation of existing hospitalization
- A persistent or significant incapacity or substantial disruption of the ability to conduct normal life functions
- A congenital anomaly/birth defect

Important medical events that may not result in death, be life-threatening, or require hospitalization may be considered serious when, based upon appropriate medical judgement, they may jeopardize the subject and may require medical or surgical intervention to prevent one of the outcomes listed in this definition.

### 6.7.3 Classification of adverse events

#### 6.7.3.1 Severity

The severity of AEs should be graded using the CTCAE version 5.0 (CTCAE).

For AE terms that are not listed in the CTCAE, the following grading system should be used:

- CTCAE Grade 1: Mild; asymptomatic or mild symptoms; clinical or diagnostic observations only; intervention not indicated;
- CTCAE Grade 2: Moderate; minimal, local, or non-invasive intervention indicated; limiting age-appropriate instrumental activities of daily living;
- CTCAE Grade 3: Severe or medically significant but not immediately life-threatening; hospitalization or prolongation of hospitalization indicated; disabling; limiting self-care activities of daily living;
- CTCAE Grade 4: Life-threatening consequences; urgent intervention indicated; and
- CTCAE Grade 5: Death related to AE.

#### 6.7.3.2 Relationship

The relationship of an AE to the administration of the study drug is to be assessed according to the following definitions:

No (unrelated, not related, or unlikely to be related)–- The time course between the administration of study drug and the occurrence or worsening of the AE rules out a causal relationship and another cause (concomitant drugs, therapies, complications, etc) is suspected.

Yes (possibly, probably, or definitely related)–- The time course between the administration of study drug and the occurrence or worsening of the AE is consistent with a causal relationship and no other cause (concomitant drugs, therapies, complications, etc) can be identified. The definition implies a reasonable possibility of a causal relationship between the event and the study drug. This means that there are facts (evidence) or arguments to suggest a causal relationship.

The following factors should also be considered:

- The temporal sequence from study drug administration-

The event should occur after the study drug is given. The length of time from the study drug exposure to the event should be evaluated in the clinical context of the event.

- Underlying, concomitant, intercurrent diseases-

Each report should be evaluated in the context of the natural history and course of the disease being treated and any other disease the subject may have.

- Concomitant drug-

The other drugs the subject is taking or the treatment the subject receives should be examined to determine whether any of them might be recognized to cause the event in question.

- Known response pattern for this class of study drug-

Clinical and/or preclinical data may indicate whether a particular response is likely to be a class effect.

- Exposure to physical and/or mental stresses-

The exposure to stress might induce adverse changes in the recipient and provide a logical and better explanation for the event.

- The pharmacology and PK of the study drug-

The known pharmacologic properties (absorption, distribution, metabolism, and excretion) of the study drug should be considered.

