#### 6.7.4.2 Serious adverse event

Collection of SAEs will only be up to 7 days following the last dose, however, follow-up on ongoing SAEs will continue until resolution or 4 weeks following the administration of the last dose of the study drug. After the 7 days reporting window, any SAE that the PI considers related to the study drug must be reported to Medpace Clinical Safety and the Sponsor/designee.

To report the SAE, complete the SAE form electronically in the eCRF. When the form is completed, Medpace Safety personnel will be notified electronically and will retrieve the form. If the event meets serious criteria and it is not possible to access the eCRF, send an email to Medpace Safety at **[contact]** or call the Medpace SAE hotline (phone number listed below) and fax/email the completed paper SAE form to Medpace (contact information listed below) within 24 hours of awareness. When the eCRF becomes available, the SAE information must be entered within 24 hours of the system becoming available.

The PI must continue to follow up the subject until the SAE has subsided or until the condition becomes chronic in nature or stabilizes (in the case of persistent impairment) or the subject dies.

Within 24 hours of receipt of follow-up information, the PI must update the SAE form electronically in the eCRF and submit any supporting documentation (eg, subject discharge summary or autopsy reports) to Medpace Clinical Safety via fax or email. If it is not possible to access the eCRF, refer to the procedures outlined above for initial reporting of SAEs.

Safety contact information Medpace Clinical Safety

Medpace SAE hotline – USA:

[contact], dial “3” or [contact], dial “3”

[contact] or [contact]

Email: [contact]

Medpace SAE hotline – Europe:

[contact]

[contact]

Email: [contact].

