#### 7.4.2.1 Breaking the blind

The PI is responsible for the medical care of subjects during the study. In an emergency, when knowledge of the subject’s treatment assignment is essential for the clinical management or welfare of the subject, the PI can unblind the treatment information for the subject through the IRT system. The unblinding should only occur for the subject in question if it is critical for treatment decision making by the PI for the well-being of the subject.

Prior to unblinding the subject’s treatment assignment, the PI should assess the relationship of an AE to the study drug (yes or no). In the vast majority of cases, AEs may be properly managed without the need for unblinding. If unblinding is warranted, the PI must then follow the appropriate procedures to unblind an individual subject’s treatment assignment. Generally, blinding should only be broken for events that are considered to be serious, unexpected, and causally related to the study drug, or as requested by the regulatory authority.

If the study blind is broken, the PI must detail the date and reason for unblinding in the subject’s records. The PI must also notify the Sponsor and if applicable, the regulatory authority, that the study blind has been broken. If the blind is broken due to an AE, the AE form must be completed and reported to the Sponsor.

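### The relatedness definitions in Section 6.7.3.2 leave two of four combinations of timing and other cause unclassified, and the no-other-cause condition conflicts with the section's own reasonable-possibility standard

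*Protocol*

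**What the plan says.** All references are to the protocol.

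**Definitions (Section 6.7.3.2).** *Yes* covers possibly, probably and definitely related events. It requires a time course that "is consistent with a causal relationship and no other cause (concomitant drugs, therapies, complications, etc) can be identified". *No* covers unrelated, not related and unlikely related events. It requires a time course that "rules out a causal relationship and another cause (concomitant drugs, therapies, complications, etc) is suspected". In each definition the two conditions are joined by 'and'.

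**Gloss on *Yes* (same paragraph).** "The definition implies a reasonable possibility of a causal relationship between the event and the study drug". A list of factors to consider follows, including concomitant drugs and underlying disease.

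**Form of the answer (Section 7.4.2.1).** The investigator's assessment before unblinding is yes or no. No third class is defined anywhere.

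**Where the answer is used.**
- Section 6.7: discontinuation applies to an AE "considered by the PI to be possibly, probably, or definitely related to study drug and that is severe or medically significant". The enrollment halt then builds on it: "In the event that 3 subjects experience the same AE meeting the criteria described above". A second halt needs two subjects with the same life-threatening AE attributed to study drug.
- Section 8.2.1.1: one listed circumstance for suspension or termination is "3 subjects develop the same CTCAE Grade 3 AE determined as related to study drug". Another is two subjects with related Grade 4 AEs.
- Section 6.7.4.2: once the 7-day window has closed, "any SAE that the PI considers related to the study drug must be reported".
- Section 7.4.6: related TEAEs have their own summary table.

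**The concern.** A two-way classification should place every event in exactly one class, and these definitions do not. An event with compatible timing in a subject who also has another identified cause, such as a newly started medicine, fails *Yes* because of that cause. It fails *No* because timing does not exclude the drug. Yet it is the sort of event that the label possibly related is normally meant to hold.

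The paragraph also sets two standards for *Yes*. A reasonable possibility that the drug contributed can coexist with a competing cause; a requirement that no other cause can be identified cannot. The factor list tells the investigator to weigh other causes, while the definition makes an identified one a bar.

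At stake is the reproducibility of the relatedness call. The trial expects about 20 + 5 = 25 subjects on active drug across both cohorts, and the triggers are counts of two or three subjects, so the coding of a single event can decide whether a count is reached. Causality is assigned by the investigator under this protocol, so an analysis plan cannot repair the assignment afterwards.

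**Working it through.** The plan states no figure on this point, so there is none to reproduce. The check is a logical table, followed by a trace of where the result is used.

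**1. Classify the four combinations using the definitions in Section 6.7.3.2.**

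| Timing | Other cause | Meets *Yes*? | Meets *No*? | Class |
|---|---|---|---|---|
| Compatible | None identified | Yes | No | *Yes* |
| Compatible | Identified | No (other cause) | No (timing) | None |
| Ruled out | Suspected | No (timing) | Yes | *No* |
| Ruled out | None | No (timing) | No (no other cause) | None |

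Two of four combinations have no class.

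**2. Apply the gloss to the second row.** If reasonable possibility governs, an event with compatible timing and another identified cause can be *Yes*. If the no-other-cause condition governs, it cannot. The same paragraph supports both readings.

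**3. Trace the dependence on relatedness.**

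| Depends on the call | Does not depend on the call |
|---|---|
| Discontinuation for severe or medically significant related AEs (6.7) | Withdrawal from study drug for Grade 4 or higher, or for development of an AE (4.5.2) |
| Three-subject and two-subject enrollment halts (6.7) | Grade 5 circumstance (8.2.1.1) |
| Grade 3 and Grade 4 circumstances (8.2.1.1) | Sponsor and Medical Monitor review of aggregate safety data (8.2.1.1) |
| SAEs arising after the 7-day window (6.7.4.2) | SAEs up to 7 days after the last dose (6.7.4.2) |
| Related-TEAE table (7.4.6) | Tables of all TEAEs, SAEs and TEAEs by severity (7.4.6) |

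**4. Direction and sensitivity (illustration; p and f are assumptions, not figures from the documents).** Let n be the subjects on active drug, p the per-subject risk of the same qualifying AE with compatible timing, and f the share of those AEs with another identified cause. If every such event is left out, the number counted is Binomial(n, p(1 − f)). For n = 20, p = 0.20, f = 0.50 the counted rate is 0.10, and P(at least 3) = 1 − 0.9^20 − 20 × 0.1 × 0.9^19 − 190 × 0.1^2 × 0.9^18 = 0.323.

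| n | p | f = 0 | f = 0.25 | f = 0.50 | f = 0.75 |
|---|---|---|---|---|---|
| 20 | 0.10 | 0.323 | 0.186 | 0.075 | 0.013 |
| 20 | 0.20 | 0.794 | 0.595 | 0.323 | 0.075 |
| 25 | 0.10 | 0.463 | 0.288 | 0.127 | 0.024 |
| 25 | 0.20 | 0.902 | 0.746 | 0.463 | 0.127 |

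The f = 0 column also describes full use of the reasonable-possibility reading, under which no event is lost. The other columns are the fully literal extreme for the given f. The table shows that a three-subject count is sensitive to the reading; it does not estimate what will happen in this trial.

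**The case against.** The strongest reply is that the loss of events is inferred. An event in the second row fails *No* as clearly as it fails *Yes*, and an investigator forced to choose could code *Yes*. The word possibly, the reasonable-possibility sentence and the list of factors to consider all support that choice. This stands, and it limits the consequence: the documents support inconsistent coding, with a lower related count wherever the literal test is used. They do not establish that such events are always lost.

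A reader might go further and infer that the safety triggers will fire late or not at all. The documents do not support that. The circumstances in Section 8.2.1.1 are examples that may warrant action, not an exclusive list, and the routes in the right-hand column of the trace operate whatever the relatedness call. Section 8.2.1.1 also gives the sponsor its own determination that a Grade 5 event or SUSAR may be related, so the investigator's answer is not the only gate there.

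Nor do the documents show that another cause is almost always present. Eligibility requires good health apart from PASC and excludes other explanations for fatigue. A conceivable alternative is also not the same as an identified one, so the unclassified group may be narrower than it first looks.

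None of this closes the gap. The reply works only by setting aside an explicit condition of the *Yes* definition, and nothing tells the investigator to do so.

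**Conclusion.** The point holds as a defect of definition. Two of four combinations are unclassified, and the no-other-cause condition contradicts the standard stated in the same paragraph. This follows from the text alone and needs no assumption.

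The consequence is conditional. The same event can be coded either way depending on which sentence the assessor follows, and literal use can only lower the related count. The inputs affected are those in the left-hand column of the trace. How many events are involved cannot be derived from the documents, and the probabilities shown rest on assumed rates. The treatment comparison of all TEAEs is unaffected.

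The correction should be made because small relatedness-based counts rest on this call.

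**What to change.** Reconcile the two definitions in Section 6.7.3.2 so that every AE falls in exactly one class, on the standard the section already states. For example:
- *Yes*: timing is compatible and there is a reasonable possibility that study drug caused or contributed to the event, whether or not another cause is also possible.
- *No*: every other AE.

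Keep concomitant drugs, underlying disease and the other listed factors as matters to weigh in judging whether the possibility is reasonable, not as a bar to *Yes*. Under this wording an event with compatible timing and another identified cause is decided on judgement, and an event whose timing excludes the drug is *No* with or without another cause.

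No trigger count, grade threshold or stopping rule needs to change. The cost is two definitions, matching eCRF completion guidance and a retraining note for the site. The small downside is that somewhat more events may be coded as related.
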